#### fMRI data analysis

The fMRI data will be analyzed with MATLAB 2 017b (MathWorks Inc., Natick, MA, USA). After data preprocessing, amplitude of low-frequency fluctuation (ALFF), functional connectivity (FC), and large-scale functional brain network analysis, etc. will be conducted to investigate the difference of central responses between acupuncture and moxibustion. In voxel-based analysis, the threshold will be set to *p*<0.01 in voxel-level and *p*<0.05 with false discovery rate in cluster-level. While in connectome-based analysis, the threshold will be set to *p*<0.05 with false discovery rate corrected. Furthermore, the Pearson correlation analysis between the clinical results and fMRI results will be conducted to investigate the potential correlation between symptom improvements and brain activity changes elicited by different interventions.

## Discussion

This randomized control fMRI trial will compare the differences in clinical effects and the central responses between acupuncture and moxibustion. The results might deepen our understanding of the advantages and central mechanisms of acupuncture and moxibustion for FD and besides provide a reference for a better selection of interventions for treating FD.

### The similarities and differences between acupuncture and moxibustion

Acupuncture and moxibustion are two important external therapeutic methods in traditional Chinese medicine (TCM). Both of them are guided by meridian and acupoint theory, but their manipulation is different. Acupuncture is a kind of mechanical stimulation with inserting specific needles into the acupoints for lifting, thrusting, and twisting, while moxibustion is to place moxa or moxa stick directly or indirectly on an acupoint to produce a warm stimulation; Therefore, they are different and related in clinical practice. For example, a multicenter RCT showed that 4 weeks of acupuncture can significantly increase patient-reported adequate relief and improve FD symptoms and QoL, and the effects of acupuncture persisted through the 12-week follow-up without symptom relapse or rebound [11]. Besides, some trials demonstrated that moxibustion can also relieve dyspeptic symptoms and improve QoL of FD patients, as well as has a significantly instant regulating effect on the abnormal electrogastrogram (EGG) rhythm of FD patients [42, 43]. However, what are the advantages of acupuncture and moxibustion in improving symptoms and QoL? Are the underlying mechanisms of acupuncture and moxibustion different and in what ways? These issues remain unclear and worthy of investigation. To explore the therapeutic advantages of acupuncture and moxibustion for FD, this study selected five questionaries to evaluate FD patients from three aspects. First is using SF-LDQ, SID, and NDSI to assess the symptom improvement. Second is using NDQLI to evaluate the QoL. Third is investigating the psychological status by SAS and SDS.

To explore the similarities and differences in potential mechanism, the MRI  scans will be performed on the selsected patients in each group, and the HRV tests will be performed on all the patients, at the baseline and the end of the treatment. Using 24-h dynamic ECG, the HRV changes of FD patients in each group will be calculated to investigate the influence of acupuncture and moxibustion on the function of the autonomic nerve. By MRI scan, the cerebral activity changes will be analyzed to explore the brain responses to acupuncture and moxibustion, respectively. In addition, by correlation analysis, the correlations among HRV changes, cerebral activity alteration, and clinical variables improvement in each group will be used to further explore the characteristics in the pattern of central responses to acupuncture or moxibustion.

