In Roma IV criteria, FD is defined as a disorder of brain-gut interaction [12]. Therefore, exploring the pathological characteristics and therapeutic effect targets of FD from the perspective of brain activity arouses increasing attention in the past two decades. By neuroimaging techniques including PET and MRI, people found that FD patients have significant cerebral functional abnormalities and structural alterations, and the cerebral changes are related to their symptoms [13–17]. For example, our previous studies indicated that the anterior cingulate cortex (ACC), insula, thalamus, middle cingulate cortex (MCC), and cerebellum might be the key regions that were close to the severity of dyspepsia symptoms [18, 19]. Furthermore, studies have suggested that acupuncture treatment can effectively modulate the abnormal cerebral activities to improve dyspepsia symptoms and QoL, and moxibustion treatment also can elicit the cerebral signal changes in FGIDs patients [19–22]. These studies provide the possibility to explore the different therapeutic mechanisms between acupuncture and moxibustion from the central responses. Based on our previous studies, the present study is conducted to (i) evaluate the therapeutic advantages of acupuncture and moxibustion treatment for FD, (ii) investigate the similarities and differences in cerebral activity elicited by acupuncture and moxibustion, and (iii) analyze the possible correlations between the brain responses and clinical variables thus to explore the potential central mechanism of acupuncture and moxibustion respectively.

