### Data analysis

#### Clinical data analysis

All analyses will be done on the ITT population. An independent statistician will conduct clinical data analysis with SPSS 24.0 software (SPSS Inc., Chicago, IL, USA). Kolmogorov–Smirnov test will be used to analyze data distribution, and Levene’s test will be used to analyze homogeneity of variance. The quantitative variables will be presented as mean and SD or median and interquartile, whereas qualitative measures will be reported as percentages with 95% CI. Analysis of variance (ANOVA) test will be used with Bonferroni post hoc comparisons for continuous variables. The independent-samples *t*-test or the Mann-Whitney *U* test for continuous variables and the chi-square test, Fisher exact test, or Kruskal–Wallis test for categorical variables will be used, when suitable. We will describe 24-h HRV using time-domain measurements. Time-domain indices of HRV quantify the amount of variability in measurements of the interbeat interval (IBI), which is the time period between successive heartbeats. These values may be expressed in original units or as the natural logarithm (Ln) of original units to achieve a more normal distribution [41]. Pearson's coefficient will be used for bivariate correlations. All the statistical significance threshold tests will be set to *p*<0.05 with a two-tailed test.

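### Brain–symptom and HRV–symptom correlations are planned arm by arm, with no between-arm test of them and no stated multiplicity correction, although the article asks whether the mechanisms differ

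*Protocol article*

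**What the plan says.** The third aim, in the Background, is to "analyze the possible correlations between the brain responses and clinical variables thus to explore the potential central mechanism of acupuncture and moxibustion respectively". The Discussion subsection on the similarities and differences between the two therapies then asks: "Are the underlying mechanisms of acupuncture and moxibustion different and in what ways". It introduces the imaging and HRV measurements as the means of exploring that question, and ends with the correlation step: "the correlations among HRV changes, cerebral activity alteration, and clinical variables improvement in each group will be used to further explore the characteristics".

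The methods fix the technique in two places.

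- Under Clinical data analysis, Pearson's "coefficient will be used for bivariate correlations", and the next sentence covers significance: "All the statistical significance threshold tests will be set to" a two-tailed p<0.05. Rank-based alternatives are offered there for group comparisons but not for correlations. A log scale is allowed for HRV.
- Under fMRI data analysis, the voxel-based maps are thresholded "with false discovery rate in cluster-level", and the connectome analyses are also corrected by false discovery rate. The correlation step follows: "the Pearson correlation analysis between the clinical results and fMRI results will be conducted to investigate the potential correlation". No threshold or correction is given for it.

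The same fMRI section does plan a direct between-arm contrast. ALFF, connectivity and network analyses "will be conducted to investigate the difference of central responses between acupuncture and moxibustion".

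**The concern.** Two different questions can be asked about mechanism. One is whether the brain (or autonomic) response differs between therapies; the planned imaging contrast addresses it. The other is whether the relation between that response and symptom improvement differs. Only the correlations bear on the second question, and they are laid out separately by arm with nothing that compares them.

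That layout invites a reader, or the eventual authors, to set two lists of significant correlations side by side and treat the mismatches as different mechanisms. Two separate within-arm tests do not test a difference. With samples of this size, identical links will often give a mismatch by chance.

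Many index-by-score pairs per arm, with no declared family, also make some chance findings likely. The article says its results should help in choosing between the two treatments, so a spurious contrast in mechanism could carry weight.

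**Working it through.** **The plan's own figure.** The article gives no sample size or precision for the correlations. Its one calculation concerns the primary outcome and reproduces: pooled SD = √((2.81² + 2.62²)/2) = 2.717; d = (5.62 − 3.56)/2.717 = 0.758; the two-sample t calculation at 90% power gives 37.56, so 38 per arm and 76 in all. It says nothing about correlations.

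**Inputs.**
- fMRI subset: 36 per arm planned, with 30 as a working minimum (Sample size calculation).
- HRV: measured in all patients, so up to 46 per arm; three named indices, SDNN, SDANN and RMSSD (Heart rate variability test).
- Six clinical scores: SF-LDQ, SID, NDSI, NDQLI, SAS, SDS (Discussion).
- Two-sided α = 0.05 per test (Clinical data analysis).
- Assumed: true correlations of 0.3 to 0.4, since the article gives none.

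**1. How often do equal links look different?** By Fisher's z, the power of one within-arm test is approximately p = 1 − Φ(1.96 − atanh(ρ)·√(n − 3)). With the same ρ in both arms, the chance that exactly one arm is significant is 2p(1 − p). For example, with ρ = 0.3 and n = 36: 0.3095 × 5.745 = 1.778, p = 0.428, and 2 × 0.428 × 0.572 = 0.49.

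| n per arm | ρ | power p | one arm significant only |
|---|---|---|---|
| 30 | 0.3 | 0.363 | 46% |
| 30 | 0.4 | 0.595 | 48% |
| 36 | 0.3 | 0.428 | 49% |
| 36 | 0.4 | 0.682 | 43% |
| 46 | 0.3 | 0.528 | 50% |
| 46 | 0.4 | 0.793 | 33% |

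The 46-per-arm rows apply to HRV–symptom correlations if nobody is lost. A valid direct test of difference would be falsely significant in 5% of trials.

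**2. How many false positives?** From what the article names: 3 HRV indices × 6 scores × 2 arms = 36 tests. Under a global null, 36 × 0.05 = 1.8 are expected. The chance of at least one is 1 − 0.95³⁶ = 84% if the tests are independent.

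Once brain regions enter, the count is an assumption, because no regions of interest are declared. The range is:
- SF-LDQ only, 5 regions, 2 arms: 10 tests, 0.5 expected, 40% chance of at least one.
- 1 region against 6 scores and 3 HRV indices, plus the 18 HRV–score pairs: 27 per arm, 54 tests, 2.7 expected, 94%.
- 5 regions on the same basis: 63 per arm, 126 tests, 6.3 expected, 99.8% if independent. A simulation with correlated variables gave about 99%.

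**3. What could a direct test detect?** The difference of two Fisher z values has SE √(2/(n − 3)): 0.246 at 36 per arm and 0.272 at 30. Power at two-sided 0.05, before any multiplicity correction:
- ρ 0.5 against 0: 0.549/0.246 = 2.23, so 61% at 36 per arm; 52% at 30.
- ρ 0.5 against 0.2: 0.347/0.246 = 1.41, so 29% at 36 per arm; 25% at 30.
- About 80% power at 36 per arm needs roughly 0.6 against 0.

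**The case against.** The strongest reply is that the correlations are not where the between-arm mechanism question is decided. The second aim covers similarities and differences in cerebral activity, and the fMRI section gives it a direct analysis with false discovery rate control. The correlations belong to the third aim, are worded throughout as exploratory, and are introduced as an addition that describes each therapy in turn. This stands: a reader might infer that the mechanism conclusions rest wholly on arm-specific correlations, and the article does not support that.

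Three further points also stand.

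- Nowhere does the article say it will declare a difference because a correlation is significant in one arm and not in the other. The 43–49% measures what would happen if someone read the results that way.
- A reader might infer that every correlation is tested at an uncorrected 0.05. The general rule sits in the clinical section, directly after the Pearson sentence, so it covers the HRV–symptom correlations. For the fMRI–symptom step the text is silent, and an analysis plan not shown may fill the gap.
- The article does not predict skewed scores. It lists distribution checks and alternatives for use when suitable, so the point about rank correlations is minor.

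What the reply does not remove is that the per-arm structure and Pearson's coefficient are fixed in this document, under an opening that promises to explore differences in mechanism. The imaging contrast cannot tell whether a brain change relates to symptom relief differently in the two arms. Exploratory wording lowers the stakes but does not make a comparison of p-values valid.

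**Conclusion.** The point holds in a limited form. The plan has no analysis that could show a difference between therapies in the brain–symptom or HRV–symptom link, and it states no multiplicity correction for the correlations. If such a difference were read from the per-arm results, equal true correlations of 0.3 to 0.4 would look discordant in about 43–49% of trials, for any one measure, at 30–36 per arm. The HRV–symptom family alone carries 1.8 expected false positives under the null.

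These figures rest on the assumed correlations and on Fisher's approximation; the 84% also assumes independent tests. Counts that include brain regions are illustrative, so it would go too far to say that the brain correlations are certain to yield false positives. The primary SF-LDQ comparison and the planned imaging contrast between arms are unaffected. This is an inexpensive improvement to an exploratory aim, not a flaw in the main result.

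**What to change.** In the fMRI data analysis section, and in the Discussion paragraph that describes the per-group correlations:

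- For each declared brain or HRV measure, fit one model on both arms: symptom change on measure change, arm and their interaction, with the baseline score as covariate.
- Base any claim that the link differs between therapies on the interaction only. It compares slopes; a Fisher z test would compare the correlations themselves and could be reported beside it.
- Declare the family of measures and scores in advance and apply false discovery rate control across it.
- Report each arm's r with a 95% CI as descriptive and hypothesis-generating, using Spearman's coefficient where scores are skewed.

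The cost is a little more analysis work and fewer nominally significant correlations; no new data are needed. The real limitation is power. Taking the Fisher z figures as a guide to the interaction, it is about 61% for 0.5 against 0 and 29% for 0.5 against 0.2 at 36 per arm, and lower after correction. Only large differences could be detected, and the text should say that a non-significant interaction is not evidence of a shared mechanism.

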### Quality control approaches are the precondition for the result reliability

To improve the reliability of the results, strict quality control will be conducted in the following aspects: (i) the selection of FD patients. To avoid the influence of age, and handedness on cerebral function and structure, right-handed and aged 18 to 40 years patients will be recruited. (ii) Acupuncture and moxibustion manipulation. Two experienced registered Chinese Medicine acupuncturists will perform the manipulation with a standard operating procedure and the *deqi* sensation of acupuncture and moxibustion will be recorded. Furthermore, to quantify and control the dosage of moxibustion, a novel portable moxibustion stick (13±1g; 60mm × 4.1mm; Bozhou Aikeshu Medical Co., Ltd., China) will be used in this study, which can be easily fixed on an acupoint to burn for 30 min with a relatively stable temperature. (iii) MRI scan. All MRI scans will be performed in the morning by the same operator, and female patients will be performed during the same menstrual cycle. Twenty-four hours before scanning, participants will be asked to maintain their routine lifestyle, avoid staying up late, smoking, and drinking coffee or tea. Before being scanned, every patient will stay at a restroom for 30 min and keep calm without thinking. During scanning, patients will be required to keep their eyes closed and their ears plugged. To eliminate head motion, the participant’s head will be placed in the head mask, and a sponge will be used to strengthen the fixation of the head.

In summary, acupuncture and moxibustion are safe and effective for FD. However, the characteristics of these two therapies for treating FD remain uncertain. With the development of neuroimaging technology and analytical methods, it is possible to further investigate the advantages and the underlying mechanism. The results will provide a new perspective to understand the different clinical values of acupuncture and moxibustion for FD, and their central mechanism.

## Trial status

Currently, the trial is not yet in the process of patient recruitment. We plan to start patient recruitment in August 2021 and end in October 2022.

## Abbreviations

FD: Functional dyspepsia
FGIDs: Functional gastrointestinal disorders
SF-LDQ: Short form Leeds Dyspepsia Questionnaire
NDI: Nepean Dyspepsia Index
SID: Severity Index of Dyspepsia
SAS: Zung Self-Rating Anxiety Scale
SDS: Zung Self-Rating Depression Scale
HRV: Heart rate variability
fMRI: Functional magnetic resonance imaging
